## Abstract

**Background:**

Keshan disease is an endemic cardiomyopathy of undefined causes. Being involved in the unclear pathogenesis of Keshan disease, a clear diagnosis, and effective treatment cannot be initiated. However, the rapid development of gut flora in cardiovascular disease combined with omics and big data platforms may promote the discovery of new diagnostic markers and provide new therapeutic options. This study aims to identify biomarkers for the early diagnosis and further explore new therapeutic targets for Keshan disease.

**Methods:**

This cohort study consists of two parts. Though the first part includes 300 participants, however, recruiting will be continued for the eligible participants. After rigorous screening, the blood samples, stools, electrocardiograms, and ultrasonic cardiogram data would be collected from participants to elucidate the relationship between gut flora and host. The second part includes a prospective follow-up study for every 6 months within 2 years. Finally, deep mining of big data and rapid machine learning will be employed to analyze the baseline data, experimental data, and clinical data to seek out the new biomarkers to predict the pathogenesis of Keshan disease.

**Discussion:**

Our study will clarify the distribution of gut flora in patients with Keshan disease and the abundance and population changes of gut flora in different stages of the disease. Through the big data platform analyze the relationship between environmental factors, clinical factors, and gut flora, the main factors affecting the occurrence of Keshan disease were identified, and the changed molecular pathways of gut flora were predicted. Finally, the specific gut flora and molecular pathways affecting Keshan disease were identified by metagenomics combined with metabonomic analysis.

*Trial registration*: ChiCTR1900026639. Registered on 16 October 2019.

## Background

Clinically, Keshan disease (KD) is characterized by myocardial injury and symptoms of cardiovascular diseases, such as heart failure and cardiac dysfunction [1]. Though it is prevalent in China for 80 years, however, the highest mortality and disability rate has been reported during the 1950s to the 1980s [2]. The most frequent occurrence area of KD is reported in Shaanxi province, where 29 districts including 236 villages of 6 cities are affected, with about more than 3.1 million population at risk [3, 4].

KD is an endemic cardiomyopathy with unknown etiology in China. After years of efforts, remarkable effects have been achieved in comprehensive prevention and control of KD, however, multifarious problems remain elusive [5] i.e., (1) The etiologies and pathogenesis of KD have not been fully elucidated, therefore, the hidden dangers of KD re-epidemic still exist [6]; (2) The detection rate of “dilated cardiomyopathy” (“DCM”) in KD-inflicted area is remarkably higher than that in non-disease area [3]. “DCM” showing cardiac enlargement might not be a valid dilated heart disease. Yet, it is unclear to differentiate DCM from KD [7] which impedes the development of effective and normative treatments of KD, particularly, chronic Keshan disease (CKD). CKD is a severe illness with high mortality and poor prognosis [8, 9]. However, the transformation mechanism of the latent Keshan disease (LKD) to the CKD remains unknown [10]. Hence, these above-mentioned issues regarding KD require urgent attention to be addressed.

International and domestic researchers have attempted to explore the pathophysiological process of KD from many different perspectives, such as environmental factors, nutrition, family epigenetic susceptibility, and so on [10–12]. Although up to now, the pathogenesis of KD remains unclear. Certainly, a treatment plan without a clear etiology may fail of remission and can lead to poor prognosis. Intriguingly, with in-depth research on cardiovascular diseases and intestinal microecology, the relationship between cardiovascular diseases and gut flora has been gradually recognized. Particularly the evidence that gut flora has affected the progress of cardiovascular diseases such as hypertension, coronary atherosclerosis, and heart failure will help researchers to predict the roots of KD. Considering the fact, we anticipate that gut flora may provide a new direction for the treatment of cardiovascular disease. Thus, KD is attributed to cardiovascular disease with complicated etiology and tends to be affected by environmental factors, lifestyles, diet habits, and genetic factors. Concurrently, these factors further are known to affect the distribution, function, and metabolism of gut flora as well [13, 14]. Intriguingly, since 2000, our team has been extensively studying the molecular genetics, gene polymorphism, gene methylation, and other changes of KD, as well as the effects of low selenium on myocardial mitochondrial proteomics and cardiac structure and function [12, 15–19]. In summary, we provide a pioneer and a comprehensive definite basis for the KD research.

Here, we established the KD baseline data database, biological sample bank, and clinical data sample bank. We attempted to set up this study from a novel perspective, commencing with the distribution and metabolic status of gut flora of KD. It will couple with proteomics, metabolomics, and metagenomics with final validation by implicating the big data analysis technology to dig deeply into the relationship between gut flora and KD. Hence, considering these above approaches, we are attempting to provide valuable contributions in the discovery of biomarkers and a comprehensive pathological mechanism of KD.

## Method/design

### Study aim

The purpose of this study is as follows: At first, we aim to elucidate the basic characteristics of gut flora in patients with KD and clarify the relationship between gut flora and the development of KD; The second part is designed to explore novel biomarkers for the diagnosis of KD; Finally, we determine that the combination of gut flora function analysis tools and the big data analysis platform. And most of all, the most likely etiology of KD can be predicted and analyzed, providing a new target for the treatment of KD.

### Study design

#### The initial phase

In this part, our team consists of cardiologists, epidemiologists, pathologists, nutritionists, sports medicine doctors, geneticists, and nurses. Epidemiologists supervise the reliability of the entire study and will be responsible for regular monitoring of progress research (Fig. 1). Depending on the age distribution of patients, the next step will be conducted to screen out the suspected patients with KD, LKD, CMD, normal persons from wards, and DCM, normal persons from non-wards as our participants (Table 1), and then to conduct the systematic sampling with the 1:1 sex ratio.

**Fig. 1 Fig1:**
[figure not shown]
Flow chart of study design

**Table 1 Tab1:** The source of the object of study

Disease-prone areas (case)				Non-ward areas (case)	
Suspected KD (50)	LKD (50)	CKD (50)	Normal ward control (50)	DCM (50)	Normal non-ward control (50)

Moreover, as part of our study design, in-ward and non-ward consultations will be made every 6 months in 2 years to collect baseline data and clinical samples of participants, simultaneously. Whereafter, these data will be uploaded to the confidential database along with the application of a remote diagnosis and treatment system for daily consultation and follow-up of participants.

#### The follow-up phase

The follow-up events will be conducted by a cardiologist and a nurse (Fig. 1). There will be two types of follow-up, one is a fixed free clinic twice a year, which will be carried out in detail according to the initial stage operation process; the other will be to ask the participant’s recent physical status by phone or WeChat every month (Fig. 1). All the data of follow-up and return visits will be accurately uploaded to the big data platform in a timely and accurate manner. The results will be evaluated and confirmed by three physicians. When the participants will be back in the clinic on schedule, we will inform the patients and interpret the results of the examination and the physician’s assessment reports. However, if the participants will not be able to come to the center due to unavoidable factors, the test report will be sent to them by mail and over the phone consultation by a cardiologist.

### Study objects

This study will recruit 300 participants among which 200 participants will be from Keshan disease-prone areas in Shaanxi Province and the other 100 participants were from five non-ward areas through a random consultation. This cohort will include the suspected KD (50 cases), LKD (50 cases), CKD (50 cases), normal ward control (50 cases), DCM (50 cases), and normal non-ward control (50 cases) (Table 1). According to our estimation, the final sample size could reach about 300 participants. The recruitment will start from January 1, 2020, to December 31, 2020, and the participants with satisfying eligibility criteria will be included in our study.

### Eligibility criteria

#### Inclusion criteria

Participants should be between the age of 18 and 70 years old.The participant should have lived in the current place for at least 1 year and have no immigration plan for the next few years.Suspected KD and KD patients will be preliminarily diagnosed and grouped by cardiovascular physicians according to the clinical diagnostic criteria of KD (WS/T 210–2011) and the severity of the disease.Patients with DCM after initial diagnosis will be divided into groups by cardiovascular physicians according to the clinical diagnostic criteria of DCM.

#### Exclusion criteria

Participants having any mental or physical disability.Participants having a history of coronary artery bypass, percutaneous coronary intervention, and positive angiography report.Participants with diabetes, hypertension, thyroid disease, gastrointestinal diseases, major organ injury, mental illness, tumors, and infectious diseases.Pregnant or lactating women.Participants with a history of using any type of antibiotics or probiotics within 1 month.The participants who will refuse to continue will be excluded.

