### Study visit

#### The first part

*Step 1* Collection of baseline data

Blood and stool samples will be obtained from participants to ensure whether they conform to the fasting instructions on the day of the program. Whereafter, the selected participants should sign an informed consent form. The organizer will then assign each participant with a special digital identification barcode. This bar code will be the unique identification of the participants and will accompany them throughout the entire study. However, this bar code will not mention the grouping thus participants.*Step 2* Sample collection

The blood samples will be collected in duplicate (Table 2). One tube of 5 ml (without anticoagulant) will be used to separate the serum for biochemical and mass spectrometry. Whereas the other tube of 2 ml blood (plus EDTA-2k anticoagulant) will be used to separate the plasma for brain natriuretic peptide (BNP) testing. Aliquoted serum and plasma should be stored at − 80 °C.

**Table 2 Tab2:** Data collection using different methods at baseline

Questionnaires	Instruments	Blood sample	Stool
General questionnaire (in 10 sections)	ECG (electrocardiograph and heart rate) UCG (ultrasonic cardiogram) Physical activity questionnaire (IPAQ) Sphygmomanometer (blood pressure)	Hematological parameters (CBC)	Gut flora
Physical activity questionnaire (IPAQ)	Waist, hip, and wrist circumference	Biochemical parameters (total cholesterol, HDL cholesterol, LDL)	
Psychological status questionnaire			
Nutritional habits questionnaire (FFQ based on domestic foods)	Height scale and digital scale for weight	DNA extraction	

*HDL* high-density lipoprotein cholesterol, *LDL* low-density lipoprotein cholesterol

Stool (about 20 g) samples will be collected into an airtight container by the subjects themselves and then divided by the nurse and stored at − 80 °C for mass spectrometry and intestinal microflora analysis (Table 2).*Step 3* A questionnaire survey

After breakfast, participants will fill out a general questionnaire, physical activity questionnaire (IPAQ), psychological status questionnaire, and nutritional habits questionnaire (FFQ based on domestic foods) (Table 2).*Step 4* Functional testing

The parameters including index height, weight, wrist, waist, hip circumference, blood pressure, electrocardiograph (ECG), and heart rate, and ultrasonic cardiogram (UCG) functions will be obtained in this step (Table 2).

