A professional physician will evaluate the above results. However, it will be further reviewed by a cardiologist to confirm the diagnosis and to recommend any necessary suggestions or requests to repeat the procedure.

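### The coronary exclusion names only bypass, percutaneous intervention and positive angiography, so known infarction or angina without an angiogram is not listed as excluded

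*Protocol article*

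**What the plan says.** The coronary criterion in the Exclusion criteria is "Participants having a history of coronary artery bypass, percutaneous coronary intervention, and positive angiography report". Each item records an investigation or treatment that has already taken place.

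The criterion after it works by disease: "Participants with diabetes, hypertension, thyroid disease, gastrointestinal diseases, major organ injury, mental illness, tumors, and infectious diseases". Coronary heart disease, angina and infarction are not on that list.

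The Background gives the reason why this matters for the exposure under study: "gut flora has affected the progress of cardiovascular diseases such as hypertension, coronary atherosclerosis, and heart failure".

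The age rule is "Participants should be between the age of 18 and 70 years old". The cardiac tests at baseline (Study visit, The first part) are described as "blood pressure, electrocardiograph (ECG), and heart rate, and ultrasonic cardiogram (UCG) functions will be obtained in this step". Neither that section nor Table 2 lists coronary imaging or a stress test. On review of the results the article says that "it will be further reviewed by a cardiologist to confirm the diagnosis". KD patients are grouped "according to the clinical diagnostic criteria of KD (WS/T 210–2011) and the severity of the disease" and DCM patients are "divided into groups by cardiovascular physicians according to the clinical diagnostic criteria of DCM". The content of those two sets of criteria is not reproduced.

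**The concern.** The protocol treats two conditions differently although its own rationale puts them side by side. Hypertension is excluded as a diagnosis. Coronary atherosclerosis is excluded only where an angiogram or a revascularisation has documented it. A person managed medically for an infarction or angina, with no angiogram, falls under neither criterion by name.

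At stake are the gut-flora comparisons set out in the Discussion: across normal ward participants, suspected KD, LKD and CKD, and between KD and DCM. If coronary disease itself goes with a different flora, as the Background implies, coronary cases left in the cohort add variation that has nothing to do with Keshan disease. If they are more frequent in one group than in another, part of a group difference could be coronary in origin.

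**Working it through.** **1. Reading the criteria.** Take a participant with a known infarction or angina and no angiogram.
- Coronary criterion: no bypass, no percutaneous intervention, no positive angiogram. Not excluded.
- Disease criterion: no coronary diagnosis is listed. Major organ injury might be stretched to cover an infarction, but the article does not define it. Not clearly excluded.
- Baseline tests: ECG and echocardiography may show an old infarction. They do not establish coronary disease in general, and no rule says that such a finding leads to exclusion.

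So the gap exists in the text.

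**2. Group sizes.** The article states six groups of 50: 6 × 50 = 300, with 4 × 50 = 200 from disease-prone areas and 2 × 50 = 100 from non-ward areas. These totals reproduce. The article states no power calculation.

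**3. How many cases could remain (illustration only).** Let p be coronary prevalence before exclusion and f the share of coronary cases that the criterion catches. Prevalence among those enrolled is p(1 − f)/(1 − pf). The article gives neither p nor f, so both are assumed. Expected cases per 50 enrolled:

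| p | f = 0 | f = 0.2 | f = 0.5 | f = 0.9 |
|---|---|---|---|---|
| 2% | 1.0 | 0.8 | 0.5 | 0.1 |
| 5% | 2.5 | 2.0 | 1.3 | 0.3 |
| 10% | 5.0 | 4.1 | 2.6 | 0.6 |
| 20% | 10.0 | 8.3 | 5.6 | 1.2 |

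Example: p = 10%, f = 0.2 gives 0.08/0.98 = 8.2%, or 4.1 of 50.

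The same table shows what a wider criterion does: it raises f. At p = 10%, going from f = 0.2 to f = 0.5 lowers the remaining cases from 4.1 to 2.6 per 50. It does not bring them to zero.

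**4. When this becomes a difference between groups.**
- Same p and same f in two groups: same residual, no imbalance.
- Same p, f of 0 against 0.9: the gap runs from 1.0 − 0.1 = 0.9 cases per 50 (p = 2%) to 10.0 − 1.2 = 8.8 per 50 (p = 20%).
- Same f, p of 5% against 20%: the gap is 10.0 − 2.5 = 7.5 per 50 at f = 0 and 5.6 − 1.3 = 4.3 per 50 at f = 0.5.

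**5. Possible effect on a comparison.** Assume that coronary disease shifts a flora measure by one standard deviation (SD). A gap of 8.8 per 50 is 8.8/50 = 0.18, so the difference in group means moves by about 0.18 SD. A gap of 0.9 per 50 moves it by about 0.02 SD. The standard error of a difference between two groups of 50 is √(1/50 + 1/50) = 0.20 SD. Even the largest gap for equal p, under a one-SD shift, stays below one standard error. A larger shift would scale the effect in proportion.

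**The case against.** The strongest reply is that the article has other filters. Every participant has ECG and echocardiography, with cardiologist review. The Study design section requires controls to be normal persons, which someone with known angina does not plainly satisfy. Diabetes and hypertension are excluded outright. The cited KD and DCM criteria may already require ischaemic disease to be ruled out. This is also a condensed article, and the full protocol may define the exclusions more closely. Much of this stands: these filters may remove some of the cases, especially among controls. None of them is stated to exclude coronary disease, however, and the published list is explicit about what it does name.

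A reader might infer more than the text supports, in three ways.
- **That coronary disease enters some groups more than others**, for example because DCM patients are investigated more than villagers with KD. The article gives no angiography rate and no coronary prevalence for any group. Cardiovascular physicians diagnose and group both KD and DCM patients. An imbalance is possible, but neither its existence nor its direction is shown, and any ratio between groups would rest on invented inputs.
- **That the word *and* means all three items are needed for exclusion.** The next criterion joins its diseases in the same way and plainly means any one of them. This is ordinary list grammar.
- **That a coronary pattern would be mistaken for a Keshan disease pattern.** Under the one-SD assumption in the working, the effect is modest even in an extreme scenario.

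It is also fair to say that a physician's diagnosis depends on access to care, as an angiogram does. A wider criterion narrows the gap but does not fully equalise detection between groups.

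**Conclusion.** The narrower point holds. The coronary criterion works only through documented procedures or angiography, while hypertension, which the Background sets beside coronary atherosclerosis, is excluded by diagnosis. Known infarction, angina or coronary heart disease without an angiogram is not named as excluded, and what remains may confound the gut-flora comparisons.

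The size cannot be derived from the article. Under the assumed ranges above, 0.1 to 10 cases per 50 would remain, before any removal by the baseline tests and the cited diagnostic criteria. Imbalance across groups is a possibility, not a finding. Silent disease cannot be removed by any rewording. This is a cheap improvement to an eligibility rule, not a defect that undermines the study.

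**What to change.** Reword the criterion as any one of: previous myocardial infarction; physician-diagnosed angina or coronary heart disease; coronary artery bypass; percutaneous coronary intervention; positive angiography report. Apply it identically in all six groups, from the history taken at screening.

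Add one yes/no field for whether coronary angiography was ever done. Use it in a sensitivity analysis of the KD–DCM and KD–control comparisons. With 50 per group the cells will be small, so treat that analysis as descriptive. Tabulating the field by group would also show whether earlier work-up really differs between them.

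Add to the Limitations that silent coronary disease remains possible and that detection by diagnosis still depends on access to care.

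Cost: a changed sentence, one data field and slightly more screen failures, mainly among older participants. No new procedure is needed.

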### Data management and analysis

A research assistant will review the integrity and quality of the data to upload to the big data platform. The uploaded data will be further reviewed by the epidemiologists of the Clinical Research Center for Endemic Disease of Shaanxi province. Whilst unqualified data will be reacquired. Of note, the data output will be checked weekly.

Simultaneously, all the data will be uploaded to the official website of the Chinese Clinical Trial Registration Center for review. Based on previous findings and recommendations of the Health Services Standards Research Committee, baseline data and hybrid models will be analyzed in different categories and time-to-event analyses will be performed on subsequent data. Multiple inputs will be applied to deal with missing values.

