## Limitations

The fact that KD has a complicated etiology, therefore, it is difficult to distinguish its clinical symptoms from those of DCM.Limitations of this study include selection bias, as it includes only 18 to 70-year-olds and only the Chinese population, which may lead to the need to confirm the results of multinational studies.Of note, presently we do not know how many participants will continue to participate or leave this study, due to various reasons i.e., relocation, refusal to join, and other diseases and deaths. If there is a loss, we will immediately find the cause and remedy it. If it cannot be remedied, we will follow the last-observation-carried-forward (LOCF) method. Moreover, we will follow up with the participants to ensure the continuity of the data.

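### An exclusion criterion removes participants who later refuse to continue, so the analysed cohort depends on conduct after entry, and for refusers it conflicts with the loss-handling rule under Limitations

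*Protocol article*

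**What the plan says.** Under Eligibility criteria, the exclusion list ends with "The participants who will refuse to continue will be excluded". The other items describe a person's state or history at entry, such as comorbidity, pregnancy or recent antibiotic use.

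Three other places in the protocol article bear on people who leave:

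- **Limitations** says that "presently we do not know how many participants will continue to participate or leave this study". As reasons it names moving away, refusal, other illness and death. It promises to look for the cause of a loss and remedy it, and then adds: "If it cannot be remedied, we will follow the last-observation-carried-forward (LOCF) method".
- **Data management and analysis** says: "Multiple inputs will be applied to deal with missing values". This appears to mean multiple imputation. The same section says that "time-to-event analyses will be performed on subsequent data".
- **Recruitment** makes taking part conditional on agreement and a signed consent form.

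On size, Study objects states: "This study will recruit 300 participants among which 200 participants will be from Keshan disease-prone areas in Shaanxi Province". Table 1 sets out six groups of 50. Follow-up visits take place every 6 months for 2 years. Blood, stool, electrocardiogram and ultrasonic cardiogram data are collected in the first part, before that follow-up.

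**The concern.** An eligibility criterion should be decidable at entry. This one depends on something that may happen at any time in the following two years. Followed as written, it allows a later event to decide who counts as a member of the cohort.

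Two parts of the study are exposed:

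- **Baseline part.** The first study aim is to describe gut flora in Keshan disease. A stool sample taken at entry is as informative from someone who stops at month 12 as from someone who stays. Making inclusion depend on later attendance costs precision, and may select the groups, with no gain.
- **Cohort part.** The outcomes include progression, severe heart failure and death. If willingness to continue is related to health, restricting the analysis to those who stay distorts the risks. Person-time and events observed before the refusal would also fall out.

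There is also an inconsistency. Carrying the last observation forward requires the leaver to be in the analysis set, and an excluded participant is not. Two analysts working from the same article could build different datasets.

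**Working it through.** **1. The stated sample size.** From Table 1, 6 × 50 = 300. Disease-prone areas give 4 × 50 = 200 and non-ward areas 2 × 50 = 100. The stated total is reproduced. The article gives no power, significance level, effect size or loss rate, so no power-based derivation of 300 can be tested.

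**2. The rules side by side, for a participant who is enrolled, gives baseline samples and refuses at month 12.**

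| Section | Treatment of this participant |
|---|---|
| Exclusion criteria | Excluded |
| Limitations | Loss to be remedied; failing that, last observation carried forward, so retained |
| Data management and analysis, missing values | Filled in, so retained |
| Data management and analysis, time-to-event | No rule for withdrawal |

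The direct conflict is between the first two rows. For a participant lost through relocation, other disease or death, the first row does not apply and there is no conflict.

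**3. Loss of precision in a two-group baseline comparison.**

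Inputs: 50 per group (Table 1). Assumed, because the article does not give them: two-sided 5% (z = 1.960), 80% power (z = 0.842), refusal of 5% to 30% spread evenly over the groups, and no replacement.

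Detectable standardised difference = (1.960 + 0.842) × √(2/n), where n = 50 × (1 − refusal rate).

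With no refusal: 2.802 × √(2/50) = 2.802 × 0.200 = 0.560.

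| Assumed refusal | Mean n per group | Total | Detectable difference (SD) | Power for 0.56 SD |
|---|---|---|---|---|
| 0% | 50 | 300 | 0.560 | 80% |
| 5% | 47.5 | 285 | 0.575 | 78% |
| 10% | 45 | 270 | 0.591 | 76% |
| 20% | 40 | 240 | 0.626 | 71% |
| 30% | 35 | 210 | 0.670 | 65% |

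The standard error rises by √(50/40) − 1 = 12% at 20% refusal and by √(50/35) − 1 = 20% at 30%.

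**4. Direction of bias in a risk.** Let p be the true risk, a the refusal proportion among those who have the event and b the proportion among those who do not. With refusers excluded, the reported risk is

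p(1 − a) / [p(1 − a) + (1 − p)(1 − b)].

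This equals p when a = b, is too low when a > b and too high when a < b. The article gives none of p, a or b, so the size cannot be calculated from it.

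**The case against.** **The sentence may refer to screening.** Study visit, Step 1, describes obtaining samples first and signing consent afterwards, so a person could decline to go on before enrolment, and leaving that person out would be ordinary. This reading is open, but the text does not state it. Recruitment already makes consent a condition of taking part, so the sentence would then add little. This supports clarifying the sentence, not leaving it as it is.

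**The article never says that samples or data are discarded.** This is correct. A reader might infer that baseline samples are destroyed, but the documents do not say so. The supportable statement is that, read literally, refusers fall outside the analysis.

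**The contradiction does not cover all leavers.** This also stands. A reader might infer contradictory rules for everyone who leaves, but the exclusion concerns refusal only. Limitations speaks of refusal to join, which taken alone could mean non-enrolment, but it lists this among reasons for continuing or leaving, so an overlap for refusers is a fair reading. The time-to-event sentence gives no withdrawal rule and so contradicts nothing.

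**A bias figure cannot be charged to this sentence.** A reader might assume 20% leavers at twice a 20% risk, obtain 0.8 × 0.20 + 0.2 × 0.40 = 24%, and blame the exclusion for reporting 20%. That compares exclusion with complete observation of leavers. Keeping follow-up to last contact would not recover 24%, because events after leaving stay unseen. The risks are also invented, and a rate of all leaving is not a rate of refusal.

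**Refusers might be replaced.** The Abstract says that recruiting will be continued, and Study objects expects a final sample of about 300. Replacement would reduce or remove the loss of precision in step 3. It would not remove the selection on staying. Study objects also ends recruitment on 31 December 2020, while follow-up lasts 2 years, so many refusals could come after that date.

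**Conclusion.** The point holds as a defect in a stated rule. A post-entry event is listed as an eligibility exclusion, nothing limits it to screening, and for participants who refuse it conflicts with the carry-forward rule under Limitations.

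At 5% to 30% refusal without replacement, 15 to 90 of the 300 participants would be lost to baseline comparisons that they could validly inform, and the detectable difference would rise by 0.015 to 0.110 SD. At the low end this is small. The refusal rates, power and significance level are assumptions. Bias in the cohort risks arises only if refusal is related to outcome, and no size can be given for it.

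The matter should be settled before the analysis set is fixed, because the sentence decides who is analysed in both parts of the study.

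**What to change.** 1. Delete the sentence from the exclusion criteria, or limit it expressly to people who decline before enrolment.
2. State that participants who later refuse stay in the baseline analysis and contribute follow-up until their last contact, as far as their consent to use of the data allows.
3. Reconcile this with Limitations, so that one rule applies to refusers throughout the document.
4. Report by group how many participants stopped, and compare the baseline characteristics of stoppers and stayers.

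The cost is a few sentences in the protocol and one descriptive table; no further data collection is needed. The limit of the repair should be acknowledged: censoring at withdrawal may still be informative, so it preserves what was observed and makes dropout visible, but does not remove all dropout bias.
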